## 3.3. Recruitment of participants

The company representatives and/or the principal investigator will visit study sites and meet with the employees, if possible in small groups, to explain the purpose and rough procedures of the study to increase interest for this program beforehand.

Every month CRC will send out invitation letters and questionnaires to 200 employees, of whom 50 will be candidates (K6>=9), of whom 50 will be interviewed with CIDI by [name] and [name], of whom 40 will be eligible, of whom 30 will give the final informed consent. These 30 will be randomized to active treatment (n=10) or to waiting list (n=20). Nine telephone counselors will then have to initiate telephone CBT with 1-2 clients every month.

We will repeat this process for 9 months or until we recruit 100 clients in the telephone CBT arm.

The long wait-list and unequal allocation is defensible and explained by the limited number of competent telephone counselors available. The 9 counselors can start treating only 1-2 clients every month, i.e. 3-4 clients simultaneously at any given time (because one course of telephone CBT lasts 2-3 months); in order to recruit 100 clients, this means that 9 months of recruitment will be necessary for the 9 counselors. Those on the waiting list can receive the telephone CBT only after 15 months.

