### 3.1.2. Exclusion criteria

1. Part-time employees
2. Sick leave for 6 or more days for a physical or mental condition in the past month
3. Expected to be on pregnancy leave, maternity leave or nursing leave within 2 years after screening
4. Current treatment for a mental health problem from a mental health professional
5. Major depressive episode in the past month, as ascertained by CIDI [We do not exclude dysthymia or major depression in partial remission]
6. Lifetime history of bipolar disorder, as ascertained by CIDI
7. Any substance dependence in the past 12 months, as ascertained by CIDI. [We do not exclude substance abuse.]
8. Any other current mental disorder if it constitutes the predominant aspect of the clinical presentation and requires treatment not offered in the project

We will have a registry of all the candidates at Office X and Factory Y (approximately 1200 regular or temporary employees altogether) of this company to whom we will send the invitation letter, and compare those who give the full consent to participate in the intervention trial to the original population, to examine the generalizability of our results.

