## 3.2. Sample size assumptions and estimates

A systematic review of psychological treatments, mostly CBT, for subthreshold depression yielded a Cohen’s d of 0.42 (95%CI: 0.23 to 0.60) at post-test and 0.16 (95%CI: 0.02 to 0.35) at 1-year follow-up (Cuijpers et al., 2007). ( a Cohen's d of .42 indicates a treatment effect (difference between control mean and intervention mean on the outcome measure) equal to 0.42 standard deviations (where standard deviation(SD) of interest if the SD of the outcome measure)

|  |  |  | 1:1 |  | If 1:2 |  | If 1:3 |  |
| --- | --- | --- | --- | --- | --- | --- | --- | --- |
| alpha | power | Effect size | n in each cell | Total N | n in active treatment | Total N | n in active treatment | Total N |
| 0.05 | 0.90 | 0.4 | **131** | 262 | **99** | 297 | **88** | 350 |
| 0.05 | 0.80 | 0.4 | **98** | 196 |  |  |  |  |

Thus, if we randomize 99 in the intervention group and twice that many in the control group (198) for a total of 297 randomized, we will have 90% power to detect a treatment effect assuming that this difference is equal to .40 standard deviations. However, these calculations ignore dropout. We expect that 90% will complete our month 4 followup, resulting in 89 respondents in the intervention group and 178 respondents at month 4 in the control group. In this situation, we will have 90% power to detect an effect size equal to .42 SD, which is exactly equal to our best estimate of what effect we expect to see at month 4 in this trial.

At month 15, we will have inadequate power to detect treatment effects since we expect those effects to be much smaller than those seen at month 4 (only about .16 SD's). However, in order to obtain insight into the next RCT to demonstrate prophylactic effect, we will conduct 15-month follow-up. Analyses of the 15-month follow-up will be exploratory.

If we think we can recruit 300 participants, we will go for 1:2 (intervention: control) allocation. If we expect to get closer to 200 total subjects only, we will go for 1:1 allocation, because the number in the active arm is important for journal reviewers and we would then not have 100 in the intervention group under 1:2 randomization.

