### 3.3.1. Assessment of eligibility

#### 1^st^ screening and preliminary IC

We will send out the invitation letter, written consent form, and the screening questionnaires (JCQ, HPQ, K6 and face sheet asking for the name, date of birth, sex, email address/telephone number, job category, current treatment for physical condition, current treatment for mental condition, whether he/she is currently on sick leave for any reason, and whether he/she would like to receive the feedback on the questionnaire results, candidate appointment times for CIDI) to all the workers of Office X and Factory Y of the company.

Those who consent to the screening questionnaire and interview will return the signed consent form and the screening questionnaires individually.

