### 3.3.4. Intervention allocation

We will randomize eligible subjects to intervention and control groups at a ratio of 1:2. Randomization will be stratified on three variables, namely depression severity at baseline (BDI2=<19 vs >=20), absolute presenteeism prior to baseline (6 or higher vs 5 or lower, based on the obtained median of the eligible subjects in the pilot run) and center (Office X, Factory Y, Factory Z). Assuming that subjects are recruited from 3 sites, there will be a total of 12 strata. The study statistician will prepare 12 lists of random assignments ahead of time, one for each of the 12 strata. Each list will be blocked to ensure that the ratio of intervention to control is exactly 1:2 at set intervals within each stratum. The statistician will send these lists to the research assistant who is not involved in any other aspects of the study and who will build a spreadsheet that enables concealed sequential allocation and will be responsible for keeping these lists in the safe place.

Before randomizing an individual, the CRC will make a final determination of whether or not the person is eligible to be in the randomized trial. For example, prior to randomization, we will exclude those who score too low (BDI2=<9), which may well occur because of the difference between K6 and BDI2 and due to time elapsed for screening, because those who score too low at baseline will have less room for improvement. Once the CRC determines the eligibility of the participant, she will enter his/her registration number and the stratification variables to the spreadsheet which will automatically generate the allocation according to the pre-determined random sequence. The entered variables cannot be undone in order to guarantee allocation concealment.

Those randomized to control group will be put on a waiting list and after 15 months can receive the telephone CBT if they wish to do so.

One stratification factor is BDI2>=20 and BDI2<=19. This cutoff was chosen because our previous study suggests the score ranges 14-19 to be mildly ill, 20-28 to be moderately ill and 29- to be severely ill (Hiroe et al., 2005) and because our pilot study suggested that this is about the median BDI2 value for employees with K6>=9.

Another stratification factor is presenteeism, because this will be one of our primary outcomes and it is important to make sure that some effect can be seen, when in fact there is, probably among the more disturbed people.

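### The two-site invitation frame of about 1200 employees supports about 180 randomised (about 71% power at 1:2), not the planned 297, and the third site that might close the gap is neither invited nor counted

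*Protocol*

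**What the plan says.** **Frame.** Section 3.1.2 describes "a registry of all the candidates at Office X and Factory Y (approximately 1200 regular or temporary employees altogether", and these are the people who receive the invitation letter. Section 3.3.1 (1st screening and preliminary IC) sends the letter and questionnaires "to all the workers of Office X and Factory Y of the company". Neither section names another site.

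**Rate.** Section 3.3: "Every month CRC will send out invitation letters and questionnaires to 200 employees, of whom 50 will be candidates (K6>=9". All 50 candidates are interviewed, 40 are eligible and 30 consent and are randomised, 10 to CBT and 20 to the waiting list. Then: "We will repeat this process for 9 months or until we recruit 100 clients in the telephone CBT arm". Section 6.2 allows the 9 months to be extended to 12.

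**Target.** Section 3.2 plans 99 and 198 (297 in total). It allows for 90% completion at month 4 (89 and 178) and states that "we will have 90% power to detect an effect size equal to .42 SD".

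**Allocation.** Section 3.2 chooses 1:2 if about 300 can be recruited, but: "If we expect to get closer to 200 total subjects only, we will go for 1:1 allocation". Section 3.3.4 says: "We will randomize eligible subjects to intervention and control groups at a ratio of 1:2". The same section stratifies by three centres (Office X, Factory Y and Factory Z), on the assumption that all three recruit. It gives no headcount for Factory Z.

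**The concern.** Each section is coherent alone, but together they do not agree. Section 3.3 needs 1800 letters over nine months, and the only frame with a number attached holds about 1200 people. If recruitment stays within that frame, the trial ends at well under two thirds of its planned size, and the chance of missing the expected month 4 effect rises from about 10% to about 29%.

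The allocation ratio is also affected. Section 3.2 ties it to the expected total, and the two-site total is nearer 200 than 300. Extending recruitment to 12 months adds time but no employees, so it does not help if the frame is the limit.

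**Working it through.** **Inputs from the protocol**
- Frame: about 1200 (3.1.2, 3.3.1)
- Mailing: 200 a month, 30 randomised per mailing, 10 of them to CBT (3.3). Yield = 30/200 = 15%.
- Target 99:198, 90% completion at month 4, d = 0.40 before and 0.42 after dropout, alpha 0.05 (3.2). Sidedness is not stated; a two-sided test reproduces the plan's figures.

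**Power formula.** Two-sample t-test, noncentrality = d / √(1/n1 + 1/n2), with n1 + n2 − 2 degrees of freedom.

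**1. Reproduce the stated power**
- 99:198, d = 0.40: noncentrality 3.25, power 90.0%.
- 89:178, d = 0.42: noncentrality 3.24, power 89.7%.

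The 90% in section 3.2 is correctly computed for 297.

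**2. What the two-site frame yields**
- Mailings: 1200 / 200 = 6.
- Randomised: 6 × 30 = 180, as 60:120 at 1:2.
- Respondents at 90%: 54:108.
- Noncentrality = 0.42 / √(1/54 + 1/108) = 2.52, power 70.7%.
- Effect detectable with 90% power at 54:108: d = 0.54.
- The same 180 at 1:1 (90:90, respondents 81:81): noncentrality 2.67, power 75.7%.

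**3. What the plan needs**
- Nine mailings: 9 × 200 = 1800 employees, which is 600 more than the frame. They yield 9 × 30 = 270, with 90 on CBT. Respondents 81:162, power 86.7%.
- 297 randomised: 297 / 0.15 = 1980 employees, which is 780 more than the frame.
- 100 on CBT at 10 a month: 10 months, within the 12 that section 6.2 allows.

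**4. Factory Z.** Its headcount is not given, so the added employees below are assumptions. Yield is held at 15%, allocation at 1:2, retention at 90% and d at 0.42.

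| Added employees (assumed) | Randomised | Respondents | Power |
| --- | --- | --- | --- |
| 0 | 180 | 54:108 | 71% |
| 200 | 210 | 63:126 | 77% |
| 400 | 240 | 72:144 | 83% |
| 600 | 270 | 81:162 | 87% |
| 780 | 297 | 89:178 | 90% |

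**5. 1:1 against counselor capacity.** Section 3.3 sets two limits for each of nine counselors: 1-2 starts a month and 3-4 clients at a time, with courses of 2-3 months. At 1:1, 30 a month gives 15 CBT starts, and 15 / 9 = 1.7 per counselor, inside the first limit. Concurrent load is 1.7 × 2 to 1.7 × 3, about 3.3 to 5 clients, which passes the second limit for longer courses.

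**The case against.** The strongest reply is Factory Z. The figure of 1200 is explicitly the count for Office X and Factory Y, and section 3.3.4 builds 12 strata on three recruiting sites. A third site of sufficient size would close the gap. This stands as far as it goes: 180 and 71% are the two-site case, not a forecast for the trial. It does not remove the contradiction, because the sections that define who is invited leave Factory Z out and nothing says how many people work there.

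Some stronger readings are tempting but not supported:
- *The 90% is miscalculated.* It is not. Section 3.2 makes it conditional on randomising 297, and it reproduces. The fault is that the stated frame does not deliver 297.
- *1:2 already breaks the plan's own rule.* The rule turns on the expected total, and 1:2 is consistent with expecting about 300. It conflicts only on the two-site reading. Section 3.3 also defends 1:2 by counselor capacity, and step 5 shows that 1:1 may not fit that capacity.
- *The ratio would change part-way and become tied to calendar time.* Nothing in the protocol proposes such a switch.
- *The yield is overstated because BDI2 of 9 or less is removed after consent.* Section 3.3.4 places this check just before randomisation, but section 3.1.1 places BDI2 of 10 or more at the second screening. The loss may therefore already sit in the step from 50 to 40. Interviewing all 50 candidates is optimistic, not contradictory.
- *Nine months cannot give 100 on CBT.* At 10 a month they give 90, but the extension in section 6.2 covers the tenth month, so this is minor.

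**Conclusion.** The point holds as an inconsistency between sections that bears on whether the primary sample size can be reached. At the protocol's own yield, Office X and Factory Y support about 180 randomised, with about 71% power at 1:2 or 76% at 1:1, against the 90% planned for 297. With Factory Z the answer lies anywhere from about 71% to 90% for an assumed 0 to 780 further employees, and the protocol does not let a reader say where.

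These figures assume a 15% yield from every mailing, one invitation per employee, 90% retention in both arms, d = 0.42 and a two-sided 5% test.

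**What to change.** Before the first randomisation, reconcile sections 3.1.2, 3.3, 3.3.1 and 3.3.4:

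1. Either add Factory Z to the invitation frame in 3.1.2 and 3.3.1 with its headcount, and show that the total (about 1980 at the stated yield) supports 297; or restate section 3.2 with the number and power that the actual frame delivers. For the two-site case that is about 180, with 71% power at 1:2 or 76% at 1:1.
2. Apply the section 3.2 allocation rule once to that expected total. Check 1:1 against both counselor limits in section 3.3, and make section 3.3.4 agree.
3. State in section 3.3 that 100 CBT clients at 10 a month takes 10 months, within the extension in section 6.2.

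The cost is protocol wording and, if Factory Z is small or not used, a less favourable stated power. Adding Factory Z to the frame also means mailing and screening its employees.

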### 3.3.1. Assessment of eligibility

#### 1^st^ screening and preliminary IC

We will send out the invitation letter, written consent form, and the screening questionnaires (JCQ, HPQ, K6 and face sheet asking for the name, date of birth, sex, email address/telephone number, job category, current treatment for physical condition, current treatment for mental condition, whether he/she is currently on sick leave for any reason, and whether he/she would like to receive the feedback on the questionnaire results, candidate appointment times for CIDI) to all the workers of Office X and Factory Y of the company.

Those who consent to the screening questionnaire and interview will return the signed consent form and the screening questionnaires individually.

#### 2^nd^ screening

When the questionnaire is returned and the person scores 9 or more on K6, a CIDI interviewer will call him/her up and administer the CIDI. The CIDI will cover the mood disorder and substance abuse sections.

We will return the feedback based on CIDI, JCQ, HPQ and K6 to those who have asked for it.

#### Final IC

Those who scored 9 or more on K6 but did not meet diagnostic criteria for current major depression, for substance dependence in the past 12 months or for lifetime bipolar disorder will be contacted by the CRC by mail (and/or by telephone) and will be asked for further consent to participate in the intervention trial.

Those who express consent on the telephone will be sent by mail the IC explanation and consent form and the BDI2.

On the other hand, those who were found to be currently in major depressive episode will be excluded from this trial but will be contacted by the CRC, so that they would be advised to see an industrial physician or an extra-mural specialist. The CRC would explain by letter that, according to all the data accumulated so far, the subject was judged to profit more by seeing a specialist in person than by this telephone CBT.

### 3.3.2. Baseline assessments

In order for the baseline assessment to reflect the true baseline at start of intervention, we will use two prompts for the 1^st^ IC & screening questionnaire and the 2^nd^ IC and BDI2, each within 2 weeks. Those who do not respond by 3 weeks will be considered non-consenting.

The baseline assessments will therefore consist of the following variables.

#### From the questionnaires for the1st screening

1. Job Content Questionnaire 🡪 Job control, Job demand
2. Health and Productivity Questionnaire 🡪 Total hours worked for the past 4 weeks, Relative absenteeism for the past 4 weeks (% of the working hours absent), Relative presenteeism for the past 4 weeks (Effective hours worked)
3. K6
4. Date of birth
5. Sex
6. Job category
7. Current treatment for physical and/or mental conditions
8. Any sick leave in the past month
9. Expected to be on pregnancy leave, maternity leave, or nursing leave within 2 years

#### From the CIDI interview and the subsequent questionnaire:

CIDI results for mood and substance use disorders

BDI2 for the past 2 weeks

### 3.3.3. Informed consent

Written informed consent will be obtained from all participants included in this study after full disclosure and explanation of the purpose and procedures of the study. Candidates will be informed that their participation is totally voluntary, that even after voluntarily participating they can withdraw from the intervention or from both the intervention and the assessment at any time without stating the reason, and that neither participation nor withdrawal will lead to any advantage or disadvantage at the company.

Data of each participant will be handled with sequentially allocated numbers to keep the participant’s confidentiality and kept in a computer not connected to the Internet. The list of participants and their numbers will not be electronically stored but will be kept on a separate sheet stored in a safe, locked place and will be accessible to the CRC only.

The explanation for IC will emphasize the client’s susceptibility/vulnerability based on the screening data and potential benefit from the program, in order to enhance his/her adherence.

However, at the same time, we cannot oversell the program because we have the TAU condition as well.

A brochure will help. See pages 208 and 212 of Friedman, and examples from Geddes. Should be simple and in color. Avoid using the intervention name: otherwise, the participants in the control group will be demoralized. Asking for IC for questionnaire and IC for telephone CBT will, hopefully, increase patient adherence.

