# 4. INTERVENTIONS

## 4.1. Description and schedule

In order for the randomization and start of intervention to be as close as possible, CRC will endeavor to randomize the client the day after the 2^nd^ IC is returned, arrange the 1^st^ appointment and send out the appropriate manuals on the same day.

The telephone counseling makes use of a client manual and a client workbook. We have also prepared a counselor manual. All of these have been modeled after “Creating a Balance: A Step-by-Step Approach to Managing Stress and Lifting Your Mood” (Simon et al., 2006) which has been trialed in two large RCTs and found effective in alleviating major depression when combined with pharmacotherapy in the primary care (Simon et al., 2004) and in the workplace (Wang et al., 2007).

The telephone CBT consists of 8 sessions; 1 for introduction, 3 for BA, 3 for CR and 1 for summary. The contents of the program have been modified and adapted, based on the expert opinions of the PIs of this study and on the feedbacks received from clients in the pilot runs in order to make them more suitable for subthreshold depression among workers in the Japanese culture. For each session, the client has to make a preparation, receive a telephone counseling session for approximately 30-45 minutes, and subsequently do some homework.

The EAP program is the one which has already been in use by this company since 1997. The program includes a web site for mental and physical health, a p.r.n. telephone or in-person counseling service accessible to all the employees and on-site lectures on mental and physical health for managers and workers. For the year 2007, the average service provided per employee was 0.09 mental health self-check-ups on the web, 0.003 telephone counseling session, and 0.001 in-person counseling session. The company paid $3 per person per annum for this much service. In addition, Office X and Factory Y have part-time psychologists who administered 0.13 session per employee in 2006. We will not tell the providers of the EAP program about this telephone CBT trial, but at the same time we will not ask the participants to refrain from telling the EAP personnel about the trial if and when they do contact them.

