### 5.2.3. How to enhance adherence and reduce dropouts

Dropout from the intervention will be strictly distinguished and differentiated from dropout from the study. We will ask the client, so far as it is possible with him/her, that he/she respond to the final assessment even if he/she has chosen to stop the telephone counseling itself.

The explanation for IC will emphasize the client’s susceptibility/vulnerability based on the screening data and potential benefit from the program, in order to enhance his/her adherence.

A brochure (e.g. page 208, page 212 of the textbook) may help.

Taking IC twice will likely eliminate those half-hearted volunteers and/or also enhance adherence among the more determined.

We will send out New Year Cards to both the intervention and the control groups for the year 2010, which is right before the 15-month follow-up for the first cohort, and in 2011. We will send out a thank-you card after 4-month and 15-month follow-ups. It will be very good if we can give any reward, monetary or otherwise, especially to those people who respond to the 4-month [this is our primary outcome] and 15-month follow-up, but this needs to be negotiated with the sponsor.

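### The consent explanation is to stress vulnerability and potential benefit before 1:2 randomization, which can add to the control-arm demoralization that the protocol itself fears; neutral wording would be a cheap improvement

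*Protocol*

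**What the plan says.** Section 3.3.3 (Informed consent) asks that the explanation given to candidates stress their "susceptibility/vulnerability based on the screening data and potential benefit from the program, in order to enhance his/her adherence". The same sentence recurs in section 5.2.3, on adherence and dropout.

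Section 3.3.3 adds three further statements:
- A caveat: "we cannot oversell the program because we have the TAU condition as well". Section 5.2.3 does not repeat it.
- Directly after the remarks on a brochure: "Avoid using the intervention name: otherwise, the participants in the control group will be demoralized".
- At the end: "Asking for IC for questionnaire and IC for telephone CBT will, hopefully, increase patient adherence".

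The section opens by requiring that participants be told fully what the study is for and what it involves.

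On timing, section 4.1 has the coordinator aim to "randomize the client the day after the 2^nd^ IC is returned", so the explanation precedes allocation. Section 3.3.4 states: "We will randomize eligible subjects to intervention and control groups at a ratio of 1:2". It continues: "Those randomized to control group will be put on a waiting list and after 15 months can receive the telephone CBT".

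The end of section 1 describes the trial as non-blinded. Section 2.1 makes BDI2 and HPQ at 4 months the two outcomes that decide effectiveness. Section 5.3.3 says that everything apart from the CIDI is self-reported.

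**The concern.** The stated purpose of the message is adherence, and attending sessions concerns only the arm that receives them. The message nevertheless goes to everyone, because it is delivered before allocation. A control participant is told that the screening shows vulnerability, that the program may help, and then that it is not available until after month 15. Someone in that position may feel let down, or may expect to improve only once treated, and may rate mood and work performance accordingly.

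With open allocation and self-rated outcomes, nothing in the assessment separates such a reporting shift from a real effect of CBT. The ANCOVA in section 6.1.4 adjusts for baseline, so it cannot remove a shift that arises after allocation. At stake is how far a month-4 difference can be read as an effect of the telephone program.

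**Working it through.** **1. Who hears the message and then waits.** Section 3.2 plans 99 intervention and 198 control participants, 297 in all; 198/297 = 67%. Section 3.2 also keeps a 1:1 option if only about 200 can be recruited, in which case half would be controls. Section 3.3.4 fixes 1:2.

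**2. The safeguards side by side.**
- *Not overselling* (3.3.3) is an intention with no wording behind it. It stands next to an instruction to emphasize benefit, and 5.2.3 carries only that instruction.
- *Not naming the intervention* (3.3.3) may apply only to the brochure. It sits uneasily with the disclosure requirement, with a second consent that the protocol labels as being for telephone CBT, and with the offer of telephone CBT to controls after 15 months.
- *Returning the BDI2 to the coordinator rather than the therapist* (5.3.2) limits therapist influence. It does not bear on disappointment among controls.

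**3. The plan's own figures reproduce.** Assume a two-sided alpha of 0.05 and an SD of 1. With n controls and n/2 treated, the variance of the difference is 1/n + 2/n = 3/n. For 90% power at 0.40 SD:

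n = 3 × (1.960 + 1.282)² / 0.40² ≈ 197.1, rounded up to 198; with 99 treated, the total is 297, as stated.

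At 90% completion, 99 × 0.9 ≈ 89 and 198 × 0.9 ≈ 178. Then:

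SE = √(1/89 + 1/178) = 0.130 SD

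Power at 0.42 SD = Φ(0.42/0.1298 − 1.960) = Φ(1.275) ≈ 89.9%, against the stated 90%.

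The sample size is not at fault.

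**4. Illustration of a reporting shift.** The protocol gives no figure for such a shift, so b below is purely an assumption. With no true effect and control self-ratings worse by b SD:

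P(p < 0.05) = Φ(b/SE − 1.960) + Φ(−b/SE − 1.960)

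| b (SD, assumed) | b/SE | Chance of significance, one outcome | b as share of 0.42 SD |
|---|---|---|---|
| 0 | 0 | 5.0% | 0% |
| 0.05 | 0.39 | 6.7% | 12% |
| 0.10 | 0.77 | 12.0% | 24% |
| 0.15 | 1.16 | about 21% | 36% |

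An observed difference of 1.96 × 0.1298 = 0.254 SD is already significant.

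**5. The opposite direction.** If the vulnerability message instead led controls to seek help, so that a true 0.42 SD contrast shrank by 0.10 SD, power would be Φ(0.32/0.1298 − 1.960) = Φ(0.505) ≈ 69%. The document does not show which direction would prevail.

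**The case against.** The strongest reply is that the calculation says nothing specific about this sentence. Any systematic 0.10 SD shift with 89 and 178 respondents gives about 12%, whatever its source. Open allocation, the waiting list and self-report would all remain after rewording. This stands: the percentages are not what the fix would recover.

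Second, the protocol is more careful than a bare reading of the instruction suggests. It speaks of potential benefit, warns against overselling and requires disclosure. It explains the long wait by counselor capacity (3.3), leaves the EAP and hotline open to all participants (5.2.1) and sends cards to both arms (5.2.3). This also stands, but none of it says how emphasis and restraint are to be balanced.

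Third, the direction is open. Section 5.2.1 lets participants use the EAP or outside care, which could improve controls and narrow the contrast. The sentence in 5.2.3 may also be meant to keep participants in follow-up, since that section covers dropout from the study as well as from the intervention.

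A reader might infer more than the text supports:
- *That not naming the intervention cannot work.* The participant-facing wording is not available here, and the protocol's own label for the second consent does not show what candidates read. The tension is visible; failure is not shown.
- *That 15 months of waiting weigh on the primary result.* The primary outcomes are at month 4, so only the first 4 months of the wait bear on them.
- *That control dropout will rise.* Nothing in the protocol supports this.

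**Conclusion.** The point holds as a risk of bias that the protocol itself adds to and could easily reduce. The facts are in the text: an instruction to emphasize vulnerability and benefit, delivered before 1:2 allocation, in an open trial with a waiting-list control and self-rated primary outcomes. The protocol names the hazard, and one of the two sections carrying the instruction lacks the caveat.

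It would go too far to conclude that the consent wording will produce a spurious CBT effect, or to quote 12% as the false-positive rate of this trial. That figure rests on an assumed 0.10 SD shift, equal SDs, no true effect and a two-sided 5% test on one outcome. Only part of any such shift could be traced to the consent explanation. The change is worth considering because it is cheap; the validity of the design does not hang on it.

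**What to change.** In sections 3.3.3 and 5.2.3, replace the sentence on vulnerability and benefit with a neutral explanation, the same for every candidate before randomization. It should say that the benefit of this program in this population is not yet known, that both arms keep the EAP, and that data from both arms matter equally.

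Leave motivation for attending sessions to the introductory CBT session after allocation. Keep it to attendance: a benefit message sent only to the CBT arm would add an expectancy difference of its own.

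Reconcile the instruction not to name the intervention with the disclosure requirement and with the second consent, rather than simply deleting it. If it applies only to the brochure, say so, and state what the consent form will call the program.

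The cost is redrafting the explanation and brochure, with a possibly slightly lower consent rate. Sample size, allocation and analysis are unchanged. Disappointment inherent in an open waiting-list design would remain.
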